### Current trial status

The trial has been approved by the Ethics Committee of Ruijin hospital, Shanghai Jiao Tong University School of Medicine (RJ 2020–250) on 14 August 2020 and registered on ClinicalTrials.gov (NCT04517266) before recruitment. The currently used trial protocol version is Version 2.0 (December 2020). The recruitment of the trial is initiated on 10 December 2020. At present, the IMNI PRECISION trial remains at the recruiting stage and a total of 75 patients have been enrolled until 30 July 2022. We would publish the survival outcome of patients enrolled in the present trial after completing the trial and long-term follow-up.

## Discussion

Due to an increased survival benefit and decreased recurrence from adjuvant RT, adjuvant RT has become a standard treatment for early-stage BC patients. However, the application of adjuvant RT is related to an increased treatment-related morbidity and is a heavy burden for patients due to its costly and inconvenient. As a result, great efforts have been performed to minimize RT related toxicities in recent years, but most of those ongoing trials focusing on omitting adjuvant radiation in low-risk populations by using clinical-genomic model. However, whether clinical-genomic model could individually stratify the recurrence risk of pN1 breast cancer and tailor the RNI volume for those patients remains unknown. Prior to this trial, several secondary analyses of prospective trials have indicated that genomic scores, including 21-gene Recurrence Score [17, 26, 27] and PAM-50 genes [18], could be used as a prognostic tool to identify high local recurrence risk in node-negative or node positive HR-positive BC undergoing adjuvant hormonal therapy. Subsequently, prospective clinical trials, including PRIMETIME trial (NCT04916132), PRECISION trial (NCT05182437), EXPERT trial (NCT02889874) and IDEA trial (NCT02400190) et al., have been performed to investigate the prognostic role of multi-genes in guiding omitting RT among low-risk breast cancer after BCS. TAILOR RT trial (NCT 03,488,693) is the first large phase III trial to validate whether regional RT in biomarker low-risk node positive and T3N0 breast cancer could be safely omitted. However, no randomized controlled trial has been performed to guide RT in clinically high-risk BC patients presented with one to three lymph nodes positive. In this prospective study, we combine established clinical risk model with RecurIndex score to stratify the recurrence risk of pN1 BC, and classify them into two cohort. For those with clinical “high risk” and genomic “high risk”, CW/WB + comprehensive RNI with IMNI would be performed. While for those with clinical “high risk” but genomic “low risk”, patients would be randomized into omitting IMNI group or with IMNI group. In the era of precision medicine, we hope our research would provide high-level convincing evidence for IMNI for early-stage BC patients.

The current trial has several potential limitations. First of all, this is a single institute randomized controlled trial, and enrolling patients are performed at our institution, which might limit generalization of the result to other medical centers. Secondly, this is an open-label trial, both the participants and radiation oncologists are aware of the study group assignment, which might increase the selection bias. Thirdly, the primary outcome is 2-year event-free survival, and the follow-up is too short for observing events. After completing the trial, long-term follow-up of enrolled participants would be continued. Fourthly, the randomization of the present trial does not stratify according to risk factors, which might another source of heterogeneity. Finally, the 10% non-inferiority margin between the two groups might be larger in clinical practice, although this margin is discussed and decided by our clinical team.

In conclusion, the IMNI PRECISION trial is a non-inferior, randomized controlled trial to compare the survival and toxicity differences of omitting IMNI vs delivering IMNI in pN1 BC patients by using our established clinical risk model and multi-genomic model. We anticipate that our results would provide high-level evidence to tailor IMNI according to individualized recurrence risk of BC.

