### Participants

To compared the non-inferior difference of 5-year event-free survival for RNI omitting IMNI vs. RNI with IMNI group among early-stage BC with early-stage BC patients with clinically “high risk” but genomic low risk, a total of 214 patients will be recruited.

The detailed instruction of present study would be offered to every potential participant before enrollment, and each enrolled patients should sign the informed consent.

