### Outcomes

#### The primary outcomes

The primary outcome is the event-free survival, which is determined as the time from randomization to the time of a first recurrence in ipsilateral chest wall or in breast or in regional nodal or distant sites, a contralateral BC, or breast cancer specific death.

The secondary endpoints include the following outcomes: (1) local regional recurrence free survival, which is defined as the time from randomization to a first recurrence in ipsilateral chest wall or in breast or in regional nodal areas. (2) overall survival which is defined as the time from randomization to death from any cause.

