#### Power and sample size calculation

The power and sample size are calculated according to the hypothesis that the 5-year event-free survival of omitting IMNI group is non-inferior to those patients treated with comprehensive RNI with IMNI. According to survival outcome of pN1 breast cancer in our institute, the 5-year event free survival (EFS) is estimated to be 91% for the control and 81% for experimental groups, respectively. The permissible limit for HR is 2.30, with statistical power of 80%, an alpha level of 0.025 (one-sided). With an anticipated enrolment period of 24 months, a total sample size of 208 patients is estimated to be needed. To compensate for eligible patients, the targeted number of patients is set at 214.

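### The primary outcome is 5-year EFS where the trial is sized but 2-year EFS in the limitations; a 2-year readout would roughly halve an already low power

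*Protocol article*

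**What the plan says.** All references are to the protocol article.

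- **Participants** gives the aim of recruitment: "To compared the non-inferior difference of 5-year event-free survival for RNI omitting IMNI vs. RNI with IMNI group".
- **Power and sample size calculation** rests on the same horizon: "The power and sample size are calculated according to the hypothesis that the 5-year event-free survival of omitting IMNI group is non-inferior". The rates are 5-year rates: "the 5-year event free survival (EFS) is estimated to be 91% for the control and 81% for experimental groups, respectively". The margin is a hazard ratio: "The permissible limit for HR is 2.30, with statistical power of 80%, an alpha level of 0.025 (one-sided").
- **The primary outcomes** defines a time-to-event endpoint without a landmark year: "The primary outcome is the event-free survival, which is determined as the time from randomization to the time of a first recurrence".
- **Follow up** plans at least 5 years after radiotherapy for each patient, and Table 1 runs to 5 years.
- **Statistical analysis** names a Kaplan–Meier comparison of EFS and gives no analysis time.
- **Discussion**, limitations paragraph, states: "Thirdly, the primary outcome is 2-year event-free survival, and the follow-up is too short for observing events". It then places long-term follow-up after completion of the trial. It also gives the margin on another scale, with no year attached: "the 10% non-inferiority margin between the two groups might be larger in clinical practice".

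**The concern.** Two different horizons are given for the primary outcome, and they imply different analysis times and different amounts of information. The 2-year wording is hard to treat as a stray digit. The same sentence draws a consequence from it (follow-up too short for events), and the next sentence puts longer follow-up outside the trial. Together they describe a trial that reads out at about 2 years, although its rates and sample size were set for 5.

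The margin adds to the problem because it appears as HR 2.30 in one section and as 10% in another. An HR margin means the same thing at any time under proportional hazards. A 10-point difference does not: it is much more permissive early, when few patients have had events. Whether an early readout costs power or loosens the test therefore depends on which margin goes with which horizon. Patients in the experimental arm forgo a treatment that the Background describes as strongly recommended by guideline, so the answer matters.

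**Working it through.** **Inputs from the article.** 5-year EFS 91% (control) and 81% (experimental); HR margin 2.30; one-sided alpha 0.025; power 80%; 1:1 allocation; 24 months of accrual; 208 patients before allowance, 214 targeted; a 10-point margin in the limitations.

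**Assumptions.** Constant and proportional hazards, uniform accrual, no dropout. For power, true HR 1 with 91% 5-year EFS in both arms.

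**Step 1: the plan's own figure.**
- Events needed (Schoenfeld, 1:1): 4 × (1.960 + 0.842)² / (ln 2.30)² = 45.3, so 46.
- With 24 months of accrual plus 5 years, the event probability is 0.107 at 91% and 0.223 at 81%. The number needed is 431 with 91% in both arms, or 279 with 91% and 81%. Neither is 208.
- Using 81% in both arms gives 46 / 0.2232 = 206.1, or 208 after rounding to 104 per arm. This matches, but it changes the stated control rate.
- Reading 91% and 81% as 2-year rates, with accrual plus 2 years, gives 350 (91% in both arms) or 230 (91% and 81%). The arithmetic gives no support to 2 years as the intended basis.

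**Step 2: events and power on the HR 2.30 margin, N = 208.** The hazard is −ln(0.91)/5 = 0.01886 per year. For a fixed time t per patient, the event probability is 1 − 0.91^(t/5). Power = Φ(√(events/4) × ln 2.30 − 1.96).

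| Readout | Event probability | Events | Power |
|---|---|---|---|
| Exactly 5 years each | 0.0900 | 18.7 | 44% |
| Exactly 2 years each | 0.0370 | 7.7 | 21% |
| 24-month accrual + 5 years | 0.1070 | 22.2 | 50% |
| 24-month accrual + 2 years | 0.0550 | 11.4 | 29% |

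Example: √(7.7/4) × 0.833 − 1.96 = −0.80, and Φ(−0.80) = 0.21.

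If 208 was obtained with 81% in both arms, power falls from 81% (46.4 events) at accrual plus 5 years to 54% (24.6 events) at accrual plus 2 years.

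**Step 3: type I error on the HR margin.** A simulation at true HR 2.30 (104 per arm, 40,000 runs, Wald test of the rate ratio) gave 2.4% at 2 years and 2.6% at 5 years, against a nominal 2.5%.

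**Step 4: the 10-point margin, if it were moved to 2 years (hypothetical).**
- Control 2-year EFS: 0.91^(2/5) = 0.963.
- A 10-point margin allows 0.863, which is HR ln(0.863)/ln(0.963) ≈ 3.9. The matching 5-year EFS is 0.91^3.9 ≈ 69%.
- At true HR 2.30, experimental 2-year EFS is 0.963^2.30 = 0.917, a difference of 4.6 points.
- With 107 per arm, SE = √[(0.963 × 0.037 + 0.917 × 0.083)/107] = 0.0323.
- Chance of declaring non-inferiority: Φ((0.100 − 0.046)/0.0323 − 1.96) ≈ 38%. It is also about 38% with 104 per arm.
- The same 10-point test at 5 years: 0.91^2.30 = 0.805, a difference of 10.5 points, SE 0.047, chance about 2%.

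**The case against.** Most of the article points to 5 years: the aim of recruitment, the sizing hypothesis, the rates, the planned follow-up and Table 1. Current trial status adds that survival results will be published after completion and long-term follow-up. The 2-year wording occurs once, in a limitation. The article condenses protocol Version 2.0, which is not shown and may fix the analysis time. This makes 5 years the likely intention, and it means one cannot say that the readout will be chosen after open-label results are seen. It does not remove the conflict, because the limitation reasons from the 2-year horizon and does not merely mention it.

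A reader might infer that a 2-year readout would make the non-inferiority conclusion invalid. The documents do not support that. The sample size section states the margin as HR 2.30, and on that margin an early readout costs power while the false-claim rate stays near its nominal level. The 38% figure needs the 10-point margin to be applied to 2-year EFS. No section says so, and the only rates in the article that differ by 10 points are the 5-year ones.

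A reader might also set about 8 events at 2 years against the 46 needed and blame the whole gap on the horizon. That is wrong too. With 91% in both arms, 5 years yields only 18.7 to 22.2 events. Much of the shortfall is a separate sample size problem.

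**Conclusion.** The contradiction stands, and it concerns the horizon of the primary outcome. The loss attributable to a 2-year readout on the HR 2.30 margin is a fall in power from 44% to 21% (exactly 5 against 2 years each) or from 50% to 29% (24-month accrual plus 5 against 2 years). The likely consequence is an inconclusive trial. A test that is far too lenient is a conditional risk: it follows only if the undated 10-point margin is paired with the 2-year horizon named in the same paragraph. These sizes rest on constant and proportional hazards, no dropout, 208 patients and 91% 5-year EFS in both arms. The contradiction itself rests on no assumption.

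**What to change.** 1. In the limitations, replace 2-year with the 5-year EFS used in Participants and in the sample size section, and revise the remark that follow-up is too short to match.
2. State when the primary non-inferiority analysis takes place, consistent with the 5-year horizon. Waiting until every patient has 5 years of follow-up or an event is one acceptable rule. An event-driven rule is another.
3. Tie the margin to that horizon: HR 2.30, or 10 points at 5 years.
4. Report any 2-year result as descriptive, with no non-inferiority claim.

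The cost is a few sentences. Five-year follow-up is already planned, and 75 of the 214 patients had been enrolled by 30 July 2022, so the wording could be settled well before readout. The change does not repair the low power at 5 years, which needs its own review of the sample size.

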## Data Availability

The individual de-identified participant data used and/or analyzed in the current study are available from the corresponding author on reasonable request.

## Abbreviations

CW: Chest wall
WB: Whole breast
IMNI: Internal mammary node irradiation
RNI: Regional nodal irradiation
BC: Breast cancer
EBCTCG: Early Breast Cancer Trialists' Collaborative Group
RT: Radiotherapy
NCCN: National Comprehensive Cancer Network
DFS: Disease-free survival
EFS: Event-free survival
OS: Overall survival
LRR: Local regional recurrence
PMRT: Post-mastectomy radiotherapy
NSABP: National Surgical Adjuvant Breast and Bowel Project
ABCSG: The Austrian Breast and Colorectal Cancer Study Group
FFPE: Formalin-fixed and paraffin-embedded
ALND: Axillary lymph node dissection
SLNB: Sentinel lymph node biopsy
ER: Estrogen-receptor
PR: Progesterone-receptor
HER2: Human epidermal growth factor receptor 2
BCS: Breast conserving surgery
EDC: Electronic data capture
CTCAE 3.0: Common Terminology Criteria for Adverse Events version 3.0 (CTCAE 3.0)
RTOG: The Radiation Therapy Oncology Group
